### Randomization

The randomization process will be conducted using a web-based computer program. A list of random numbers will be generated by a computerized random allocation system operated by the Medical Statistics Support Team in Seoul National University Hospital. Eligible participants will be randomly assigned 1:1 to either the control group (fluid management based on the clinical information alone) or treatment group (BIS-guided fluid management along with clinical information). Randomization will be stratified based on the institution and presence of diabetes mellitus, and will utilize a randomized block design.

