### Sample size calculations

No previous report has evaluated the effect of BIS-guided fluid management on RRF in patients on PD. We therefore referred to a study showing that GFR changes over 1 year in a conventional PD solution treatment group and in a biocompatible PD solution treatment group were -16.8 ± 19.9 and 0.09 ± 40.9 l/week/1.73 m^2^, respectively
[13]. We adjusted the sample size for an estimated drop-out rate of 20% due to poor compliance, a two-sided level of significance of α = 5%, and a power of 80%, and found that 69 participants will be required in each group to find a significant difference using Student’s *t*-test. A total of 138 participants will be included in the analysis.

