### Statistical analyses

The statistical analyses will be conducted both on a per-protocol (PP) and an intention-to treat (ITT) basis. For PP analysis, all participants who complete the study will be included to evaluate the primary and secondary outcomes. For the ITT analysis, all participants who are enrolled and randomized to one of the two groups and who complete the first visit will be included.

Basic statistics will be reported in terms of mean ± SD for continuous variables, or as percentages for categorical variables. Differences between groups will be analyzed using Student’s *t*-test for continuous variables and the *χ*^2^ test or Fisher’s exact test for categorical variables. The difference in GFR between month 0 and month 12 will be compared between the two groups using Student’s *t*-test for the primary outcome. Analysis of covariance (ANCOVA) will be used to analyze the primary outcome as the secondary analysis to adjust the baseline value. Multivariate Cox proportional hazard regression models will be used to analyze the time to development of anuria. Although the institutions are mainly located in large cities, thereby limiting the likelihood of any important cluster effect, we will be sure to accommodate possible clustering in our models and analysis as required. A value of *P* < 0.05 will be considered statistically significant. All analyses will be performed using SPSS Statistics software (v21.0; IBM Corporation, Armonk, NY, USA).

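### The primary test is an equal-variance t-test although the planning SDs differ two-fold; if that ratio holds and completer numbers differ between arms, the type I error departs modestly from 5%

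*Protocol article*

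**What the plan says.** All references are to the protocol article.

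- **Primary test (Statistical analyses).** "The difference in GFR between month 0 and month 12 will be compared between the two groups using" Student's t-test. No unequal-variance version is named. ANCOVA adjusting for baseline is a secondary analysis of the same outcome, also without any provision for unequal variances.
- **Planning figures (Sample size calculations).** The one-year GFR changes in the reference trial "were -16.8 ± 19.9 and 0.09 ± 40.9 l/week/1.73 m^2^, respectively", for conventional and biocompatible PD solution in that order. The article explains why it borrowed them: "No previous report has evaluated the effect of BIS-guided fluid management on RRF in patients on PD".
- **Design settings (Sample size calculations, Randomization).** The calculation uses "a two-sided level of significance of α = 5%, and a power of 80"%, and concludes that "69 participants will be required in each group to find a significant difference using" Student's t-test. Allocation is equal: "Eligible participants will be randomly assigned 1:1 to either the control group" or the treatment group.
- **Losses.** "We adjusted the sample size for an estimated drop-out rate of 20% due to poor compliance". This is one overall figure, with none by arm. Participants who move to HD or combined dialysis, are transplanted, change institution or die leave the study (the section on treatment guidelines according to volume status). Residual renal function is scheduled only at months 0 and 12 (Table 1).

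**The concern.** The trial is sized with two clearly different SDs, yet the test fixed for the primary outcome pools them into one variance. The pooled test keeps its level under unequal variances when the two analysed groups are the same size. When they are not, the pooled variance gives too much weight to the larger group. If the more variable arm is the smaller one, the standard error is too small and the test rejects too often. If it is the larger one, the test rejects too rarely. The 95% confidence interval that goes with the test is too narrow or too wide in the same way.

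Equal allocation does not guarantee equal analysed numbers. A change score needs a month 12 value, there is no intermediate GFR measurement, and about a fifth of participants are expected to be lost.

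**Working it through.** **Inputs.** SDs 19.9 and 40.9, difference 0.09 + 16.8 = 16.89, two-sided 5%, 80% power, 20% drop-out, 69 per arm (all from Sample size calculations). Assumptions made here: normal data; the larger SD in the BIS-guided arm, following the order in which the figures are given; 110 completers in total (80% of 138 = 110.4); and the splits between arms.

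**1. The plan's own figure.** Per arm, n = (19.9² + 40.9²) × (1.96 + 0.842)² / 16.89² = (396.01 + 1672.81) × 7.85 / 285.27 = 56.9, so 57. Then 57 × 1.20 = 68.4, so 69. The stated 69 is reproduced, and it uses both SDs.

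**2. Ratio.** 40.9 / 19.9 = 2.06 for the SDs; 1672.81 / 396.01 = 4.22 for the variances.

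**3. Direction, worked for 60 control and 50 treatment completers.**
- Pooled variance: (59 × 396.01 + 49 × 1672.81) / 108 = 975.3.
- Squared standard error used by Student's test: 975.3 × (1/60 + 1/50) = 35.76.
- True sampling variance of the difference: 396.01/60 + 1672.81/50 = 40.06.
- Ratio 35.76 / 40.06 = 0.893, square root 0.945. The test's standard error is about 5.5% too small, and the critical value of 1.982 acts like 1.982 × 0.945 = 1.87.

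At 55/55 both quantities equal 2068.82 / 55 = 37.6, so there is no such discrepancy. At 50/60 the ratio is 40.10 / 35.80 = 1.12, and the test is conservative.

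**4. Type I error by simulation** (equal means; at least 400,000 null trials per split):

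| Completers, control/treatment | Student | Welch |
|---|---|---|
| 55/55 | 5.1% | 5.0% |
| 56/54 | 5.4% | 5.0% |
| 58/52 | 5.9% | 5.0% |
| 60/50 | 6.5% | 5.0% |
| 62/48 | 7.1% | 5.0% |
| 50/60 | 3.9% | 5.0% |

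Independent runs agree to about 0.1 percentage point.

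**5. Sensitivity to the SD ratio, Student's test at 60/50.** Ratio 1: 5.0%. Ratio 1.25: 5.5%. Ratio 1.5: 5.9%. Ratio 2.06: 6.5%.

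**6. How often chance alone unbalances the arms.** If each of 69 participants per arm is lost independently with probability 20%, the counts are exactly equal in about 8% of trials. They differ by 6 or more in 24% and by 10 or more in 4%. A gap of 10 or more against the more variable arm has probability 2.1%; 14 or more, 0.2%.

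**7. Power (noncentral t).** At 55/55: Student 77.9%, Welch 77.6%. For 80% power: 58 completers per arm with Student, 59 with Welch.

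**The case against.** The case against is substantial, and much of it stands.

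- **The SD ratio is borrowed.** It comes from a trial of PD solutions, and nothing in the article shows that BIS guidance would double the spread. If BIS guidance had no effect at all on GFR change, the randomised arms would share one distribution, selective loss aside, and Student's test would hold at 5% for any split. The inflation needs equal means together with unequal spread. This stands, and makes the point conditional.
- **Arm-specific loss is not documented.** The open-label design and the transfer-to-HD criterion make it tempting to infer that drop-out will differ by arm. The article lists HD transfer only as a reason for leaving and gives one overall drop-out figure. With equal drop-out rates, large gaps are rare, and averaged over chance imbalance the type I error is about 5.1%. This stands against any claim of a large effect.
- **The ITT analysis could restore 69/69, where Student's test is at 5.1%.** This stands only in part. GFR is measured only at months 0 and 12 and leavers are dropped, so equal numbers of observed change scores are not assured.
- **The form of the t-test is a detail for the SAP.** The article does not use the word pooled, and a later document might name the unequal-variance form. However, it names Student's t-test for both the sample size and the primary analysis, and that name ordinarily means the equal-variance form. The choice is stated, so it can be commented on.

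**Conclusion.** The point holds in a limited, conditional form. The named primary test does not match the variances on which the trial was sized. If the planned two-fold ratio holds and completers are unequal, the actual level lies between about 3.9% and 7.1% for splits up to 62/48 in one direction and 50/60 in the other. At 58/52 the departure is under one percentage point. If either condition fails, the level is about 5%.

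A reader might infer that the primary p-value and confidence interval will be wrong, or that any inequality in completers does real damage. The documents support neither: the SD ratio is an assumption from another intervention, no drop-out by arm is given, and small gaps matter little. Much larger imbalances would inflate the error further, but would first raise a problem of missing-data bias, which the choice of t-test does not address.

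The importance is minor. The reason to act is that the remedy is almost free.

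**What to change.** In Statistical analyses, name the Welch unequal-variance t-test as the primary test of the month 0 to 12 GFR change, and report the difference with the matching 95% confidence interval. For the ANCOVA, specify heteroscedasticity-robust standard errors (for example HC3). Fix this before any comparison by arm, so that the choice between the two forms of the test does not depend on the data.

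The cost is one analysis option: about 0.3 percentage points of power at 55 per arm, or one more completer per arm for 80% power (59 instead of 58). With unequal arms the apparent difference in power can be larger. At 60/50, Student rejects in 78.7% of simulated trials under the planned difference and Welch in 74.9%, but Student's figure is obtained at a true level of 6.5%. At 50/60 the order reverses (76.5% against 79.7%).

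The change does not correct bias from differential drop-out, which needs separate handling.

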### Outcome measures

The primary outcome is the change in GFR between months 0 and 12 after starting treatment. The secondary outcomes will include GFR measured by urine collection, calculated by the mean of the Cr and urea clearance at month 12; time to the anuric state (urine volume <100 ml/day); and fatal and nonfatal cardiovascular events, including acute myocardial infarction, stroke, unstable angina, and cardiovascular revascularization. Parameters obtained by echocardiographic measurements, such as the left ventricular mass index, E/e′ ratio, left ventricular end-diastolic pressure, left ventricular ejection fraction, left atrial volume index, and BP at month 12; parameters measured by BIS, such as the OH value, ECW, and ECW/ICW; hospitalization, cardiovascular and all-cause mortality, and transfer to HD over the course of 1 year; pulse wave velocity (PWV), type and number of PD fluid and diuretics at month 12, and laboratory findings including high-sensitivity C-reactive protein (hs-CRP), N-terminal prohormone of brain natriuretic peptide, and cardiac troponin T, will also be evaluated as tertiary outcomes.

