[23–25]. Although some studies have suggested cutoff thresholds for the definition of the OH in patients on HD and patients on PD of 2.5 and 2.0 liters, respectively
[19, 26, 27], we consider an ECW within ±1.1 liter as normal hydration.

There is a chance that patients within the same institution will be more correlated than patients between institutions. To avoid this, we will investigate for possible clustering of patients at the recruitment institution level, and will accommodate such clustering in our models and analysis as required. We also conservatively calculate the sample size, assuming a high drop-out rate, to overcome this potential problem.

A limitation of this study is that we will include both prevalent and incident patients on PD. Although a study targeting only incident patients on PD might provide more solid results, we will adjust the dialysis vintage in the multivariable analyses.

In summary, the COMPASS study is the first prospective, randomized controlled trial to evaluate the clinical usefulness of BIS-guided fluid management in patients on PD. The aim of this study is to evaluate whether BIS-guided fluid management has a beneficial effect on the decline of RRF, cardiac parameters, and cardiovascular outcomes.

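### Baseline-adjusted ANCOVA would be a better primary analysis of GFR change than the unadjusted t-test, which is valid but generally less precise

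*Protocol article*

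**What the plan says.** The Outcome measures section defines the endpoint: "The primary outcome is the change in GFR between months 0 and 12 after starting treatment". GFR at month 12 is listed separately as a secondary outcome.

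The Statistical analyses section names the primary test: "The difference in GFR between month 0 and month 12 will be compared between the two groups using Student’s *t*-test for the primary outcome". It then gives the adjusted model a supporting role: "Analysis of covariance (ANCOVA) will be used to analyze the primary outcome as the secondary analysis to adjust the baseline value". The same section makes Student's t-test the general method for continuous variables, which would include month-12 GFR.

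The Sample size calculations section sizes the trial for that t-test, at 69 per group. The Randomization section allocates 1:1 with stratification by institution and diabetes; baseline GFR is not a stratum. The article gives no reason for ranking the t-test above ANCOVA.

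**The concern.** Change in GFR is likely to be related to baseline GFR. A patient with more residual function has more to lose, and a clearance from a urine collection carries measurement error, so high baseline readings tend to be followed by lower ones. A change score fixes the coefficient of month-12 GFR on baseline at 1. ANCOVA estimates that coefficient from the data, which removes residual variance whenever the true value differs from 1.

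Two things are at stake. The first is precision, in a trial planned with little power to spare. The second is sensitivity to chance imbalance. The Discussion acknowledges that incident and prevalent patients are mixed, so baseline GFR may vary widely, and nothing in the randomisation balances it.

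There is also a smaller matter of coherence. Month-12 GFR, compared by an unadjusted t-test, estimates the same treatment effect in a third way and may differ from both analyses of change.

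**Working it through.** **Inputs from the article.** Changes over one year of minus "16.8 ± 19.9 and 0.09 ± 40.9 l/week/1.73 m^2^, respectively" (conventional and biocompatible PD solution, from the cited study); "a two-sided level of significance of α = 5%, and a power of 80"%; dropout 20%; 69 per group.

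**Inputs assumed.** The correlation rho between GFR at months 0 and 12, and equal SDs at the two times. The article gives neither.

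**1. The plan's own figure.**
- Difference: 0.09 + 16.8 = 16.89.
- Root-mean-square SD: sqrt((19.9² + 40.9²)/2) = 32.16.
- n per group = 2 × [(1.960 + 0.842) × 32.16/16.89]² = 56.9, so 57 evaluable.
- 57 × 1.2 = 68.4, so 69. The stated figure reproduces.

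**2. Power of the planned t-test.** 69 × 0.8 = 55.2, so 55 evaluable per arm. The standardised effect is 16.89/32.16 = 0.525. The noncentral t distribution gives 77.9% (78.6% by normal approximation).

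**3. Power of ANCOVA.** Let s be the common SD of GFR.
- Var(change) = 2s²(1 - rho).
- ANCOVA residual variance = s²(1 - rho²).
- Ratio = (1 + rho)/2.

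The SD of change stays at 32.16, so the standardised effect becomes 0.525/sqrt(ratio):

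| rho (assumed) | Variance ratio | Standardised effect | Power, 55 per arm |
|---|---|---|---|
| 0.5 | 0.75 | 0.606 | 88.3% |
| 0.6 | 0.80 | 0.587 | 86.2% |
| 0.7 | 0.85 | 0.570 | 84.1% |
| 0.8 | 0.90 | 0.554 | 82.0% |
| 0.9 | 0.95 | 0.539 | 80.0% |

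The gain over 77.9% runs from about 10 points down to 2.

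**4. Without the equal-SD assumption.** The general ratio is 1 - c², where c is the correlation of change with baseline. At c = 0 it is 1 and nothing is gained. If the month-12 SD is k times the baseline SD, the ratio is k²(1 - rho²)/(1 + k² - 2k·rho). Over rho 0.5 to 0.9, k = 1.2 gives power of about 78% to 83%, and k = 0.8 gives about 93% to 95%.

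**5. Validity and imbalance.** In 10,000 simulated trials per setting with 55 per arm:

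| | rho 0.5 | rho 0.7 |
|---|---|---|
| Type I error, t-test | 4.95% | 5.02% |
| Type I error, ANCOVA | 4.96% | 4.99% |
| Shift of change-score estimate per unit of baseline imbalance | -0.50 | -0.30 |
| Shift of ANCOVA estimate per unit of baseline imbalance | 0.00 | 0.00 |

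Both estimators are unbiased on average. The shift in the change-score estimate matches -(1 - rho). To give it a size: at rho 0.5 the implied baseline SD is 32.16/sqrt(2 × 0.5) = 32.16. A one-SD chance imbalance between arms is then 32.16 × sqrt(2/55) = 6.13. The estimate moves by 0.5 × 6.13 = 3.07, or 18% of the planned difference of 16.89.

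**6. Change versus month-12 GFR.** Change is month-12 GFR minus baseline. With baseline as a covariate, subtracting it from the outcome alters only the baseline coefficient (by 1). The treatment effect, its standard error and its p-value are identical for the two outcomes.

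**The case against.** The strongest reply is that nothing here is an error. Outcome, primary test and sample size agree with one another, and the test is valid under randomisation. The ANCOVA is already prespecified, and the article says which analysis ranks first. That stands: this is a choice between two valid methods.

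Four stronger readings are tempting, and the documents do not support them.

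- A reader might infer that baseline GFR is wasted. It is not: the change score subtracts it, and the secondary ANCOVA uses it as a covariate.
- A reader might infer that regression to the mean is left uncorrected. Under 1:1 randomisation it is equal in the two arms in expectation. It matters only through a chance imbalance, and the secondary ANCOVA deals with that.
- A reader might see a contradiction with the Discussion, where the authors write "we will adjust the dialysis vintage in the multivariable analyses". The promise concerns multivariable analyses, and the plan has models that can carry vintage (ANCOVA and Cox regression). A t-test is not one of them and is not said to be.
- A reader might say that several p-values for one effect leave the conclusion open. The stated ranking settles which governs, and keeping the t-test as a sensitivity analysis would also yield two.

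The objection to the power figures also stands in part. A single rho with equal SDs implies equal SDs of change in the two arms, whereas the planning values are 19.9 and 40.9. The figures therefore illustrate a direction and an order of magnitude; they do not predict the power of this trial. What the objection does not supply is a reason to prefer the less precise analysis.

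**Conclusion.** The point holds as an improvement in efficiency and robustness, not as the correction of a mistake. The primary t-test is unbiased on average with correct type I error, but it is generally less precise than the ANCOVA ranked below it, and its estimate moves with chance baseline imbalance where ANCOVA's does not.

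For assumed rho between 0.5 and 0.9 and equal SDs at the two times, the gain is about 10 to 2 percentage points of power at 55 per arm. It could be larger, or nil, because the article reports neither the correlation nor the SDs of GFR at months 0 and 12. The possible loss is small: one degree of freedom per covariate. The 2-point gap between 77.9% and the stated 80% comes mainly from how dropout was applied (57 × 1.2 rather than 57/0.8 = 72) and is a separate matter.

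**What to change.** In the Statistical analyses section, exchange the two roles. Make the primary analysis an ANCOVA of month-12 GFR (or change) on arm and baseline GFR, with the randomisation strata, diabetes and institution, as further covariates. Report the adjusted difference with its 95% CI, and keep the unadjusted t-test on change as a sensitivity analysis.

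Analyse the secondary outcome, GFR at month 12, with the same model, and state that it gives the same treatment effect as change. It need not be dropped.

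The cost is a change of wording. Both GFR measurements are already scheduled, the stated N can stay, and the Trial status section says recruitment is under way, so the change should be made and dated before any unblinded analysis.

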### Study design

The study is a multicenter, prospective, parallel-group, open-label, randomized controlled trial. It is an investigator-initiated clinical trial. The study algorithm is depicted in Figure 
1. After enrollment, clinical follow-up will be performed after 0, 2, 4, 6, 8, 10, and 12 months of treatment.

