### Inclusion and exclusion criteria

Inclusion criteria were: age between 20 and 75 years; duration of PD (automated peritoneal dialysis (APD) or continuous ambulatory peritoneal dialysis (CAPD)) >4 weeks; daily urine output >500 ml; and provision of written informed consent.

Exclusion criteria were: contraindication to bioimpedance measurement (amputation, presence of pacemaker, defibrillator, prosthesis, or metal implants); probable discontinuation of PD or receipt of kidney transplant within 1 year; hypoalbuminemia (serum albumin <3.3 g/dl); severe heart failure (New York Heart Association Functional Classification (NYHA FC) III or IV); combined dialysis modality (PD + intermittent hemodialysis (HD)); pregnancy, lactation; enrollment in other clinical trials within 1 month; uncontrolled hypertension (>160/100 mmHg with more than three anti-hypertensive medications); cardiovascular diseases (cerebral infarction, hemorrhagic infarction, acute myocardial infarction, or unstable angina) and acute infection (pneumonia, peritonitis) within 3 months prior to the trial.

Serum and urine creatinine (Cr) will be measured by the isotope dilution mass spectrometry-traceable method using a TBA 200FR Analyzer (Toshiba, Tokyo, Japan). GFR will be calculated as the average Cr and urea clearance, which is measured by urine collection
[8].

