**Figure 3 Fig3:**
[figure not shown]
**Hypovolemia management flow chart.** APD, automated peritoneal dialysis; CAPD, continuous ambulatory peritoneal dialysis.

Participants who switch to HD or combined dialysis (PD with intermittent HD), receive kidney transplantation, transfer to other institutions, or die during the study will be dropped out of the study. Investigators or research coordinators will evaluate treatment adherence and give scores for each particular item, including 1) percentage of self-reported medical records >80%, 2) percentage receiving PD solutions >80%, 3) adherence to examinations including complete blood count (CBC), chemistry, peritoneal equilibrium test, Kt/V (where K is dialyzer clearance of urea, t is dialysis time, and V is volume of distribution of urea, approximately equal to the patient's total body water), and 4) adherence to the scheduled visits.

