### Clinical and laboratory evaluations

Physical examination, medication reviews including PD solutions, fluid balance evaluation (semi-quantitative scale),. and laboratory evaluations, including CBC, electrolytes, Cr, protein, albumin, calcium, phosphorous, and fasting glucose will be conducted every 2 months.

Laboratory evaluations, including total cholesterol, triglyceride, low-density lipoprotein cholesterol, hs-CRP, hemoglobin A1C, intact parathyroid hormone, N-terminal prohormone of brain natriuretic peptide, cardiac troponin T, and weekly Kt/V_urea_, will be performed at months 0 and 12 of treatment. Echocardiography will be performed, and PWV will be measured using a Colin pulse waveform analyzer (Colin CO, Ltd, Komaki, Japan) at months 0 and 12 after treatment. The study schedule is shown in Table 
1.

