**Table 1 Tab1:** **Data collection schedule of the COMPASS study**

Parameter	Visit time (months)							
	-1	0	2	4	6	8	10	12
Demographic information	X							
Charlson Comorbidity Index	X							
Physical examination^1^	X	X	X	X	X	X	X	X
Medication review^2^	X	X	X	X	X	X	X	X
Routine laboratory data^3^		X	X	X	X	X	X	X
Special laboratory data^4^		X						X
RRF, urine volume		X						X
Compliance		X	X	X	X	X	X	X
New events^5^		X	X	X	X	X	X	X
BCM measurement								
Treatment group		X	X	X	X	X	X	X
Control group		X						X
Kt/V		X						X
Peritoneal equilibration test		X						
PWV		X						X
Echocardiography		X						X
PD solution, medication change		X	X	X	X	X	X	X

BCM*,* Body composition monitoring; COMPASS*,* Control Of fluid balance guided by body composition Monitoring in patients on PeritoneAl dialySiS trial; Kt/V*,* Calculated using single pool equation; PD*,* Peritoneal dialysis; PWV*,* Pulse wave velocity; RRF*,* Residual renal function.

^1^Includes body weight with an empty abdomen, blood pressure, pulse rate, and edema.

^2^Number of anti-hypertensive medications and diuretics and the type of PD solution.

^3^Complete blood count, electrolyte, serum creatinine, protein, albumin, calcium, phosphorous, and fasting glucose.

^4^Total cholesterol, triglyceride, low-density lipoprotein cholesterol, high-sensitivity C-reactive protein, hemoglobin A1C, intact parathyroid hormone, N-terminal prohormone of brain natriuretic peptide, and cardiac troponin T.

^5^Any new clinical event, including hospitalization and peritonitis, will be recorded during the study period.

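### Time to anuria is to be analysed by Cox regression, but only one post-baseline urine volume is scheduled (month 12), so onset is known only to within the whole year

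*Protocol article*

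**What the plan says.** - Outcome measures, repeated in the Abstract, lists as a secondary outcome the "time to the anuric state (urine volume <100 ml/day").
- Statistical analyses commits to a method: "Multivariate Cox proportional hazard regression models will be used to analyze the time to development of anuria".
- Table 1 has a separate row, "RRF, urine volume", marked at months 0 and 12 only. The Kt/V row is marked at the same two times.
- Inclusion criteria require "daily urine output >500 ml", so nobody is anuric at entry.
- Study design provides more frequent visits: "clinical follow-up will be performed after 0, 2, 4, 6, 8, 10, and 12 months of treatment".
- Clinical and laboratory evaluations lists what is done every two months: examination, medication review, a "fluid balance evaluation (semi-quantitative scale") and blood tests. Urine volume is not in that list.
- A footnote to Table 1 adds: "Any new clinical event, including hospitalization and peritonitis, will be recorded during the study period".
- The text after Figure 3 says that participants who move to HD or combined dialysis, are transplanted, change institution "or die during the study will be dropped out of the study". Table 1 has no exit assessment.

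**The concern.** The outcome is a numerical threshold on urine volume, so the event can be dated only as finely as urine volume is measured. The printed schedule has one measurement after baseline. A Cox model works from the order in which events occur, and one common measurement time gives no order. If actual visit dates are used instead, the order reflects when participants attended month 12, not when they became anuric.

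What is at stake is the meaning of a named secondary result. A figure would be reported as a hazard ratio for time to anuria when it compares month-12 status among those who stayed. Participants who left early, some possibly because urine output failed, would supply no measurement. The trial is still recruiting, and onset times that are not collected cannot be recovered later.

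**Working it through.** The article gives no anuria rate, event count, hazard ratio or power for this outcome, so there is no stated figure to reproduce. The check is of the passages against each other, followed by what the model does with such data.

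**1. Measurement times.** Post-baseline urine volumes in Table 1: 1 (month 12). Post-baseline visits in Study design: 6 (months 2, 4, 6, 8, 10, 12). With entry above 500 ml/day and one later measurement, a completer found below 100 ml/day has onset somewhere in (0, 12]. Measurement at every visit would narrow this to 2 months.

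**2. Cox regression with every event at one time.** Let d1 of n1 treated and d0 of n0 control participants be anuric at month 12, with D = d1 + d0. The Breslow log partial likelihood is

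l(b) = d1·b − D·ln(n1·e^b + n0).

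Setting its derivative to zero gives d1 = D·n1·e^b / (n1·e^b + n0), hence

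e^b = (d1/n1) / (d0/n0).

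This is the risk ratio among those assessed.

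**3. Illustration.** Event counts are assumed. The arm size of 55 is 69 × 0.8 = 55.2, rounded, and serves only as a plausible number assessed. The hazard ratio implied by proportional hazards over one interval is ln(1 − d1/n1) / ln(1 − d0/n0).

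| Events, control vs treated (of 55 each) | Risk ratio | Cox, Breslow (p) | Cox, Efron (p) | Implied hazard ratio | Logistic p |
|---|---|---|---|---|---|
| 6 vs 3 | 0.500 | 0.500 (0.327) | 0.487 (0.309) | 0.486 | 0.306 |
| 11 vs 6 | 0.545 | 0.545 (0.232) | 0.520 (0.198) | 0.518 | 0.193 |
| 16 vs 8 | 0.500 | 0.500 (0.109) | 0.461 (0.073) | 0.457 | 0.069 |
| 22 vs 11 | 0.500 | 0.500 (0.061) | 0.442 (0.027) | 0.437 | 0.024 |

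Last row, implied hazard ratio: ln(0.80)/ln(0.60) = 0.2231/0.5108 = 0.437.

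Breslow reproduces the risk ratio in every row. Efron ties come close to the implied hazard ratio and to the logistic p-value. That closeness relies on proportional hazards, which cannot be examined with one assessment time. In the last row the choice of tie method alone puts the same data on either side of P < 0.05.

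**4. Early leavers.** A participant who leaves before month 12 has no scheduled post-baseline urine volume. If such participants were censored at exit, they would be absent from the only risk set, at month 12. The article does not say how they are to be handled in this model.

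**The case against.** The strongest reply is that Table 1 may not be the whole of data collection. The two-monthly visits include a semi-quantitative fluid balance evaluation and open-ended recording of new events, and adherence scoring uses self-reported records. The urine-volume row is joined with RRF, so it may describe only the formal clearance collection, and a journal article is condensed. It stands that none of this rules out noticing anuria between visits, so to infer that onset could never be observed would go too far. But none of these items is tied to urine volume or to the 100 ml/day threshold, and the table marks two-monthly items as two-monthly. If interim volumes are in fact collected, Table 1 is wrong. Either way the passages need reconciling.

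A second reply is that the comparison between arms survives, and this is correct. A reader might infer that the outcome cannot be estimated at all, but the tied Cox fit is an interpretable contrast of month-12 status. What is lost is timing and, with Breslow ties, the hazard interpretation.

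A third concerns drop-out. A reader might apply the 20% in Sample size calculations and conclude that about 28 of 138 participants contribute nothing. The article attributes that allowance to poor compliance. It is not a forecast of transfer to HD or death, and no figure shows how many participants would become anuric and then leave. Nor does the article state that early leavers are censored as event-free. What stands is narrower: no exit urine volume is scheduled, so exit may be informative, to an unknown degree.

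**Conclusion.** The point holds as a mismatch between the named outcome, the analysis and the printed schedule. From the scheduled data, onset is known only to within 12 months, against 2 months if the existing visits were used, and the planned Cox model reduces to a comparison of month-12 anuria status. With Breslow ties its estimate is exactly a risk ratio. In the four assumed scenarios that is 0.500 to 0.545, where proportional hazards would imply 0.437 to 0.518.

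This rests on Table 1 being complete for urine volume and on month 12 being entered as one common time. The event counts are illustrative, because the article gives no anuria rate.

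The matter should be corrected but does not threaten the main conclusion. It concerns one secondary outcome, and the primary outcome (GFR change from month 0 to month 12) matches its schedule and is unaffected.

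**What to change.** Reconcile the schedule with the analysis in one of two ways.

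1. **Keep the schedule and change the outcome.** Rename it anuria at month 12 (yes/no) and replace the Cox model with a binary comparison (risk ratio or logistic regression). Limit covariates to what the event count supports: treatment, diabetes and four indicators for five institutions already make six parameters, while the assumed scenarios above have only 9 to 33 events in total. State a rule for participants without a month-12 urine volume, including those who die, and add a sensitivity analysis that counts transfer to HD as an event. *Cost:* no new measurements, but the time-to-event claim is given up and the rule for missing status has to be written.

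2. **Keep the outcome and change the schedule.** Record a daily urine volume at the existing two-monthly visits and at exit, and analyse with a discrete-time (complementary log-log) or interval-censored model. *Cost:* up to five more records per participant (months 2, 4, 6, 8 and 10), at most 5 × 138 = 690, plus one for each early exit. The burden is small if daily volumes are already written down at home and larger if they are not; the article does not say which.
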